## **6. OBJECTIVE OF CLINICAL TRIAL**

The primary objective of this trial was to assess the efficacy and safety of GV1001 0.56 mg (Group 1) and GV1001 1.12 mg (Group 2) compared to Placebo, in the treatment of patients with a diagnosis of moderate to severe AD.

### **6.1. Primary Efficacy Endpoint**

- 1) Change from baseline in the Severe Impairment Battery (SIB) score at Visit 15 (Week 24).

### **6.2. Secondary Efficacy Endpoint**

- 1) Change from baseline in Korean Mini-Mental State Examination (K-MMSE) score at Visit 15 (Week 24).
- 2) Change from baseline in Clinical Dementia Rating-Sum of Box (CDR-SOB) score at Visit 15 (Week 24).
- 3) Change from baseline in Neuropsychiatric Inventory (NPI) score at Visit 15 (Week 24).
- 4) Change from baseline in Global Deterioration Scale (GDS) score at Visit 15 (Week 24).
- 5) Change from baseline in Alzheimer's Disease Cooperative Study-Activities of Daily Living-severe (ADCS-ADL-severe) score at Visit 15 (Week 24).
- 6) Change from baseline in Clinician Interview-Based Impression of Change-Plus (CIBIC-plus) score at Visit 15 (Week 24).

### 6.3. Safety Endpoint

- 1) Adverse events
- 2) Laboratory tests (Hematological tests, Blood Chemistry, Urinalysis)
- 3) Vital signs

## 7. INVESTIGATIONAL PRODUCTS USED IN CLINICAL TRIAL

### 7.1. Outline of Investigational Products

#### 7.1.1. Investigational products (group1)

|                              |                                                                                                                                                                                                                          |
|------------------------------|--------------------------------------------------------------------------------------------------------------------------------------------------------------------------------------------------------------------------|
| Investigational product      | GV1001                                                                                                                                                                                                                   |
| Appearance                   | White freeze-dried powder in a colorless transparent glass vial                                                                                                                                                          |
| API/Dosage                   | Tertomotide hydrochloride (TertomotideHCl) 0.97 mg, 0.84 mg as Tertomotide                                                                                                                                               |
| Excipient                    | No                                                                                                                                                                                                                       |
| Vial                         | 3.5 mL disposable amount of a sterilized transparent vial (type I), sealed with a rubber stopper                                                                                                                         |
| Manufacturer                 | SAMSUNG PHARM Co., Ltd., Republic of Korea.                                                                                                                                                                              |
| Supplier                     | GemVax & KAEL Co., Ltd., Republic of Korea.                                                                                                                                                                              |
| Storage Temperature/Duration | 
 
Kept into a sealed container at -25 ~ -15°C (Frozen) / until 60 months of the manufacture date
 
                                                                         |
|                              | 
 
Kept into a sealed container at 2 ~ 8 °C (Refrigerated) / until 12 months of the manufacture date, and until 12 months after 43 months of frozen storage (-25 ~ -15°C)
 
 |
| Storage after Dilution       | The solution should be administered as soon as possible within up to 6 hours after dilution, and kept refrigerated at 2-8°C until before administration.                                                                 |

#### 7.1.2. Investigational products (group2)

|                         |                                                                                                  |
|-------------------------|--------------------------------------------------------------------------------------------------|
| Investigational product | GV1001                                                                                           |
| Appearance              | White freeze-dried powder in a colorless transparent glass vial                                  |
| API/Dosage              | Tertomotide hydrochloride (Tertomotide HCl) 1.94 mg, 1.68 mg as Tertomotide                      |
| Excipient               | No                                                                                               |
| Vial                    | 3.5 mL disposable amount of a sterilized transparent vial (type I), sealed with a rubber stopper |

|                              |                                                                                                                                                                                                                                                                                                                                  |
|------------------------------|----------------------------------------------------------------------------------------------------------------------------------------------------------------------------------------------------------------------------------------------------------------------------------------------------------------------------------|
| Manufacturer                 | SAMSUNG PHARM Co., Ltd., Republic of Korea.                                                                                                                                                                                                                                                                                      |
| Supplier                     | GemVax & KAEL Co., Ltd., Republic of Korea..                                                                                                                                                                                                                                                                                     |
| Storage Temperature/Duration | 
 
Kept into a sealed container at -25 ~ -15°C (Frozen) / until 60 months of the manufacture date
 
Kept into a sealed container at 2 ~ 8 °C (Refrigerated) / until 12 months of the manufacture date, and until 12 months after 43 months of frozen storage (-25 ~ -15°C)
 
 |
| Storage of Dilution          | The solution should be administered as soon as possible within up to 6 hours after dilution, and kept refrigerated at 2-8°C until before administration.                                                                                                                                                                         |

### 7.1.3. Investigational Reference Product(s)

0.9 % normal saline supplied by the study center.

## 7.2. Amount, Route and Duration of Administration

### 7.2.1. Amount and Route of Administration

#### 1) Treatment Group 1 (GV1001 0.56mg)

0.30mL of 0.9% normal saline is put into 1 vial and gently stirred to dissolve it.

The concentration of Tertomotide in this prepared solution is 2.8mg/mL, and 0.2 mL of the solution is taken and subcutaneously administered.

The solution should be administered as soon as possible within up to 6 hours after dilution, and kept refrigerated at 2-8°C until before administration.

#### 2) Treatment Group 2 (GV1001 1.12mg)

0.30mL of 0.9% normal saline is put into 1 vial and gently stirred to dissolve it.

The concentration of Tertomotide in this prepared solution is 5.6mg/mL, and 0.2 mL of the solution is taken and subcutaneously administered.

The solution should be administered as soon as possible within up to 6 hours after dilution, and kept refrigerated at 2-8°C until before administration.

#### 3) Control Group (Placebo)

0.30mL of 0.9% normal saline is put into 1 vial and gently stirred, and 0.2 mL of the solution is taken and subcutaneously administered.

### 7.2.2. Duration of Administration

The investigational product and placebo are subcutaneously administered by SC injection once weekly for Visits 2 to 5 (Weeks 1 to 4) and once every 2 weeks for Visits 6 to 15 (Weeks 6 to 24).

### **7.3. Production, Packaging and Labeling of the Investigational Product**

The investigational product is manufactured or purchased by the sponsor, and then supplied to the CRP of the study center.

As this clinical trial is conducted by the double-blind method, the formulation produced as a placebo of the investigational product should be the same in the appearance as each investigational product, should not be visually observed to be different from it and should not show a large difference in the weight. In addition, by attaching the same label, it should be ensured that the patient and the investigator are blinded. In order to do this, the manufacturer packs the vials filled with the investigational product and the investigational reference product into a plastic envelope so that the contents cannot be visible, and then the labeling is performed to notify about the blind damage of the investigation product and the code is generated to maintain blind.

The label of the investigational product is described in accordance with "Annex 11. Manufacturing of the Investigational Product of the Regulations on Good Manufacturing Practice." The description includes:

1. Indication of "For Clinical Trial"
2. Code name of product or generic name of main ingredient
3. Batch number or code number to identify the contents and packaging
4. The sponsor's name, address and phone number
5. Expiry date
6. Storage conditions
7. Reference code to identify clinical trial
8. If necessary, patient identification number, investigational product No., visit number

The investigational products will be subdivided and wrapped according to "7.2. Amount, Route and Duration of Administration" of this clinical trial protocol. Packaging of the investigational products to be used, pertinent to a total of 14 times per each patient from Visit 2 to Visit 15, should be prepared.

---

#### 7.4. Management of Investigational Product

- The investigational product should be stored in a sealed container and be kept frozen (-25~-15°C), and not allowed to be used without the instructions (prescription) of the principal investigator or the subinvestigator.
- The sponsor should supply the investigational product, etc. to the CRP directly in consultation with the principal investigator, and should receive and preserve a receipt.
- The Clinical Trial Pharmacist should keep and manage the investigational product, etc. so that they are not used for any purpose other than clinical trial.
- The sponsor should check the quantity and storage conditions of the investigational products during this clinical trial and take appropriate measures to ensure that the clinical trial is properly conducted.
- In order to maintain the double blind, the non-blinded Clinical Trial Pharmacist for storing and managing the investigational product, and the non-blinded person in charge of administration for preparing and administering the investigational product are separately designated and managed by each institution.
- The non-blinded Clinical Trial Pharmacist, the non-blinded person in charge of administration, and the non-blinded monitor should ensure that both evaluators and patients are kept blinded by avoiding the tasks of disabling double blindness.
- In case of the discontinuation and termination of the clinical trial, the sponsor should collect and discard the unused investigational products. At this time, the Clinical Trial Pharmacist should return the non-dispensed investigational products to the sponsor and preserve a return receipt, after consultation with the principal investigator. The container (vial) of the investigational products, which are dispensed to patients and used during the clinical trial, should be discarded independently in accordance with the guidelines of each study center.

#### 7.5. Maintenance of Blinding and Unblinding

To maintain double blind, in this clinical trial, the investigational product and the investigational reference product (placebo) will be packed so that no differences in the appearance are visibly observed between the two.

At the time when all patients have completed the trial, the unblinding can be done by performing the Database Locking. However, the information of the administration group, in case of unblinding, can be confirmed only by the sponsor and the CRO which conducts statistical analysis.

If the patient is required to be unblinded (the code is required to be opened) inevitably due to the occurrence of a serious ADR during the clinical trial; or this is deemed necessary by GemVax & KAEL Co., Ltd. for the patient's right and interest, and safety, only the unique code of the patient is allowed to be opened through the IWRS. In case unblinding is required, it can be made only for the patient by the investigator after consultation with the sponsor. The reason for unblinding and the date of unblinding should be documented and kept. The patient whose randomization code is unlocked cannot continue to participate in this clinical trial.

## **7.6. Concomitant Medications and Therapy/Prohibited Concomitant Medications and Therapy**

### **7.6.1. Allowed concomitant medications**

The following drugs are allowed to be administered concurrently over the duration of this clinical trial.

- ① The concomitant medications judged to have no effect on interpreting the results of this clinical trial among the medications taken by patients from before this clinical trial is allowed according to the investigator's judgment.
- ② The medications used transiently for the purpose of treating other diseases or adverse events can be administered concurrently after discussing with a doctor in charge.
- ③ Donepezil taken at stable doses for 3 months or more prior to screening visit should be administered concurrently without changes in doses over the duration of this clinical trial.

Information about each drug (name of product, purpose of administration, dosage, duration of administration, etc.) in case of administration of all concomitant medications (including the therapeutic drugs for other diseases or adverse events) should be recorded in detail in the case report form (CRF).

### **7.6.2. Prohibited concomitant medications and therapy**

The following concomitant medications are prohibited from screening (visit 1) to end-of-study visit.

Prohibited items are not limited to the concomitant medications and combination therapies specified below, and any medications judged by the investigator to have an effect on evaluating the efficacy of this clinical trial can also be prohibited.

If the prohibited concomitant medications need to be used for the treatment of patients over the duration of this clinical trial according to the judgment of investigators or doctors in charge

of other medical symptoms, the patients should immediately discontinue this clinical trial and this will have to be recorded in detail in the CRF.

- ① Other drugs for AD other than donepezil : Acetylcholinesterase inhibitors (rivastigmine, galantamine, etc.), NMDA receptor antagonists (memantine, etc.)
- ② Choline excitatory drugs (However, drugs for local administration such as choline agonists and pilocarpine collyrium are allowed.)
- ③ CNS stimulants (Methylphenidate, Modafinil, Pemoline, Atomoxetine)
- ④ Antidepressant drugs (tricyclic antidepressants, MAO inhibitors)
- ⑤ Typical antipsychotic drugs (Bromperidol, Chlorpromazine, Haloperidol)
- ⑥ Anticholinergic drugs (Atropine, Glycopyrrolate, Scopolamine, Homatropine, Ipratropium)  
However, the short-term use for the purpose of alleviating the symptoms of digestive system is allowed.)
- ⑦ All investigational products or medical devices not specified in this trial.
- ⑧ Use of any abused drug (including but not limited to illegal amphetamines, hemp, cocaine, illegal opiate drugs, propoxyphene, methadone, methaqualone, phencyclidine or illegal barbiturates)
- ⑨ Previous administration of all investigational vaccines for AD
- ⑩ Regular use of narcotics (for 3 days or more a week)
- ⑪ Other drugs affecting the immune system

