#### **12.1.1.1. SIB (Severe Impairment Battery)**

SIB evaluation will be conducted at Visits 2, 9 and 15.

The SIB (Saxton et al., 1990) was developed to evaluate dementia patients with severe cognitive impairment and consists of easy and simple questions. The questionnaire consists of 50 questions for the 9 items of "orientation", "social interaction", "construction", "orienting to name", "language", "memory", "praxis", "visuo-spatial ability". The scores range from 0 to 100 points, and the better the state of the patient, the higher the score.

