**12.2.8. Visit 16 (28 weeks  $\pm$  3 days; End of Trial)**

This visit will be conducted at 28 weeks  $\pm$  3 days after Visit 1.

- 1) Any change in concomitant medication will be checked in comparison to last visit.
- 2) Physical examination will be carried out.

- 3) Vital signs (blood pressure, pulse rate, respiration, and body temperature), height, and body weight will be measured.
- 4) Incidence of AEs and the details will be investigated.

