## **15. STATISTICAL ANALYSIS METHOD**

### **15.1. Statistical Analysis Plan**

#### **15.1.1. Definition of Analysis Set**

Analysis set is defined as follows:

- 1) Safety analysis set: the patients who have been randomized and undergone safety evaluation once or more among those who have been administered the investigational product at least once.
- 2) FAS (Full Analysis Set): the patients whose data of primary efficacy variable can be obtained among those who have been administered the investigational product at least once.
- 3) PPS (Per-Protocol Set): the patients who have completed this trial without violation of the protocol among those included in FAS group.

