#### **15.1.7. Handling of protocol violations**

The principal investigator and the subinvestigator should be well-acquainted with the protocol and thoroughly carry out the clinical trial procedures as specified in the protocol so that any protocol violation does not occur. In order to comply with the schedules for the administration of the investigational product and tests in this clinical trial, the investigator should take appropriate measures, such as written notification or telephone monitoring related to visit time, so that the patient can attend the visit on the date. On the other hand, the inevitable protocol violation should be handled as follows:

In case of a serious violation of the clinical trial protocol, the patient should be eliminated from the analysis (excluding PPS). Refer to the items below:

- ① In case the patient has no signed consent form.
- ② In case the patient is found to have violated the inclusion/exclusion criteria
- ③ In case the patient took the prohibited concomitant medication over the duration of clinical trial
- ④ In case the primary efficacy evaluation tests at the time of the initiation-termination of this trial were missing.

When it comes to minor protocol violations, which are judged to have no effect on the interpretation of the clinical trial results, the degrees and causes of violations or delays should be exactly recorded. Whether this affected this clinical trial will be comprehensively considered through the blind meeting prior to Database Lock, and will be included in the PPS analysis.

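### The serious-violation list in 15.1.7 counts prohibited drug use up to Week 28, so a drug started after the last SIB at Week 24 can remove a patient from the PPS

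*Protocol*

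**What the plan says.** The efficacy timetable ends at Week 24. The primary endpoint (6.1) is "Change from baseline in the Severe Impairment Battery (SIB) score at Visit 15 (Week 24"), and 12.1.1.1 states "SIB evaluation will be conducted at Visits 2, 9 and 15". In the flow chart the other efficacy scales also stop at Visit 15. Visit 16 (12.2.8) is headed as the end of the trial: "This visit will be conducted at 28 weeks". It covers concomitant medication, physical examination, vital signs and adverse events, with no efficacy scale.

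The medication rules run longer. Section 7.6.2 states "The following concomitant medications are prohibited from screening (visit 1) to end-of-study visit". If such a drug is needed, "the patients should immediately discontinue this clinical trial and this will have to be recorded in detail in the CRF".

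Two rules decide PPS membership:

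- Section 15.1.1 defines the PPS as "the patients who have completed this trial without violation of the protocol among those included in FAS group".
- Section 15.1.7 states "In case of a serious violation of the clinical trial protocol, the patient should be eliminated from the analysis (excluding PPS"), followed by a list of four items. Item 3 reads "In case the patient took the prohibited concomitant medication over the duration of clinical trial".

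Minor violations, judged not to affect interpretation, are reviewed at a blind meeting and kept in the PPS. Section 15.1.2 places the main efficacy analysis in the FAS, and 15.1.6 applies LOCF in the FAS but not in the PPS.

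**The concern.** A per-protocol set should drop patients whose departure from the protocol could have altered the measured outcome. Item 3 of 15.1.7 goes further. It also counts a drug started after the last SIB has been recorded, which cannot have changed that score.

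The exclusion may also not be neutral. The banned list opens with other Alzheimer's drugs such as memantine, rivastigmine and galantamine. Sections 14.2 and 17.5 expect patients with an unsatisfactory response to be guided to other treatment. Those sections describe care after the trial, so they do not show that switching occurs before Visit 16. They do make it plausible that a poor course by Week 24 prompts a new drug while the ban still runs. The PPS would then select on a consequence of the outcome.

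At stake is how far the PPS can serve as a check. It is the only stated efficacy analysis without LOCF, so readers will tend to compare it with the FAS result. With 24 evaluable patients planned per arm, two or three exclusions are visible.

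**Working it through.** **Step 1: the gap.** The ban ends at Visit 16 (Week 28) and the last SIB is at Visit 15 (Week 24): 28 − 24 = 4 weeks.

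**Step 2: follow one patient through the rules.** Take a patient who receives all 14 administrations, has a valid Week 24 SIB and starts memantine in Week 26.

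- 7.6.2: the drug is banned and the ban is still in force.
- 15.1.7 item 3: use falls within the trial, so it is a serious violation. The blind meeting weighs minor violations only, so it gives no way back.
- 7.6.2 also requires discontinuation, so the patient may not count as a completer under 15.1.1.
- FAS: its definition needs one administration and primary efficacy data. Both are present, and the Week 24 SIB is observed, so LOCF is not used. Nothing changes in the FAS.

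**Step 3: the plan's own figure.** Section 9.3 gives 24 evaluable patients per arm and a 20% dropout allowance: 24 / (1 − 0.20) = 30 per arm, 3 × 30 = 90. This reproduces. The point does not depend on it, but 24 per arm is used below. Section 9.3 gives no effect size, SD or power, and no rate of drug starts in Weeks 24 to 28 is given anywhere.

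**Step 4: illustration on assumed inputs.** Week 24 SIB change is normal with SD 1, higher is better, n = 24 per arm. Patients in the worst third (below the lower-third point of the placebo distribution, c = −0.4307) start a banned drug after Week 24 with probability q and leave the PPS. All others stay.

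Mean of the patients kept:

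- placebo: q·φ(c) / (1 − q/3), with φ(c) = 0.3636
- active, true effect 0.5: 0.5 + q·φ(c − 0.5) / (1 − q·Φ(c − 0.5)), with φ = 0.2587 and Φ = 0.1760

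| q | Placebo shift | Active shift | PPS difference (formula) | PPS difference (simulation) | Power (simulation) | Mean n kept, active / placebo |
|---|---|---|---|---|---|---|
| 0 | 0 | 0 | 0.500 | 0.501 | 39.6% | 24.0 / 24.0 |
| 0.10 | 0.0376 | 0.0263 | 0.489 | 0.489 | 38.1% | 23.6 / 23.2 |
| 0.30 | 0.1212 | 0.0819 | 0.461 | 0.460 | 34.5% | 22.7 / 21.6 |
| 0.50 | 0.2182 | 0.1418 | 0.424 | 0.426 | 30.6% | 21.9 / 20.0 |

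The simulation used 40,000 runs and a two-sided t-test at 5%. The difference shrinks because more placebo than active patients fall in the worst third.

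**Step 5: no true effect.**

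- Same q in both arms: the shifts cancel. The simulated difference is zero to within 0.002 SD and type I error is 4.8% to 5.0%.
- q = 0.10 on placebo and 0.30 on active: 0.1212 − 0.0376 = 0.084 SD (simulated 0.083), type I error 5.7%.
- q = 0.10 on placebo and 0.50 on active: 0.2182 − 0.0376 = 0.181 SD (simulated 0.181), type I error 9.2%.

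**The case against.** Several points on the other side stand.

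- **The main analysis is not affected.** A reader might infer that the primary result is biased, especially as the bracket in 15.1.7 is garbled enough to suggest removal from every analysis. The documents do not support that. The FAS definition in 15.1.1 has no violation condition, 15.1.2 makes the FAS the main set, and the same section's contrast with minor violations, which stay in the PPS, points to serious ones leaving the PPS. That reading is still an inference.
- **A missed Visit 16 is a weaker case.** A reader might infer that missing the Week 28 visit also removes a patient. That is not established. A missed safety visit is not among the four serious items and fits the minor class. Completion of the trial is undefined in 15.1.1: the Visit 16 heading suggests Week 28, while item 4 of 15.1.7 links the trial's termination to the primary efficacy tests, last done at Week 24. The wording is open, no more.
- **Larger figures are a worst case.** Deleting exactly the worst 5%, 10% or 20% of one arm would move its mean by φ(z)/(1 − p) = 0.11, 0.19 or 0.35 SD. Nothing in the protocol suggests so sharp a selection in a single arm.
- **The banned list is narrow.** Section 7.6.3 allows atypical antipsychotics and SSRIs with caution, so many new psychotropic drugs would violate nothing. It also names tricyclics in a way that sits uneasily with 7.6.2, so tricyclics are not a safe example.

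One might add that PPS detail is often left to the SAP or to blind review. That does not answer the point: the protocol itself fixes the ban's end, the serious list and the consequence, and its blind review covers minor violations only.

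**Conclusion.** The point holds for prohibited drug use. Item 3 of 15.1.7 with the ban in 7.6.2 reaches four weeks past the last SIB. It can remove from the PPS a patient with a valid Week 24 result, for an event that cannot have affected that result and may follow from it. This rests on reading the bracket in 15.1.7 as exclusion from the PPS.

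The size is modest and cannot be fixed from the document. If nobody starts a banned drug between Visits 15 and 16, the effect is zero. On the assumptions above, a 0.50 SD difference falls to about 0.49 to 0.43 SD when 10% to 50% of the worst third switch. A reader might infer a general risk of false positives, but with no true effect and equal exclusion there is no bias. It arises only if exclusion rates differ by arm, which blinding makes less likely. That the outcome prompts the drug start is plausible, not documented.

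This is a correction worth making to a supporting analysis set. It does not challenge the primary analysis.

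**What to change.** Make two changes to the analysis rules:

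- **15.1.7 item 3:** for PPS membership, count prohibited drug use only from Visit 1 up to the Visit 15 efficacy assessment. At the same time, reword the bracket to say plainly which set the patient leaves.
- **15.1.1:** state that completing the trial, for the PPS, means having the Visit 15 efficacy assessment, since the present wording can be read as requiring Visit 16.

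Later drug use or a missed Visit 16 is recorded for safety only. Whether the ban should run to Week 28 is a clinical matter for the sponsor and is not touched.

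The cost is about one sentence in each section. No data, visits or patients are added, and the sample size stays at 24 evaluable and 30 randomised per arm. The change should be made before unblinding.
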